## 2. Materials and methods

### 2.1. Study design

This is an exploratory cross-sectional observational study using VR technology to assess the performance accuracy of different hand gestures. An HMD will be used to immerse participants in the virtual environment. Motion trackers, attached to the hands and elbows, will provide participants with real-time upper body tracking (see section VR apparatus for more details). Data from the HMD and motion trackers will be continuously stored on a computer for analyses. We plan to recruit 60 schizophrenia patients and 60 age and gender matched controls over a 2-year period. The duration of the study is ~6 h. The assessments are separated into 2-h sessions/per day and all assessments are completed within a 72-h period.

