### 2.6. Secondary outcomes

We will include additional non-verbal communication tasks outside of VR to assess participants' ability to recognize and perceive non-verbal social cues such facial expressions, biological movements, and voice tone. Motor, cognitive and community functioning domains will be assessed using well-established standardized rating scales and symptom severity and antipsychotic medication usage in all patients will also be accounted for. All clinical, motor, socio-cognitive and community functioning assessments can be found in Table 2.

**Table 2 T2:** Clinical, motor, socio-cognitive and community functioning assessments of participants.

**Secondary outcomes**	**References**

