## 3. Statistical analysis

Measurements collected from the tracking devices during gesture performance will be analyzed using linear mixed models. These will include upper body rotational data per gesture across all experimental blocks. Data are saved at a frequency of 60 Hz (16 ms). The rotational data between participants and the virtual agent performing the gestures will be compared across time based on distance metrics such as Dynamic Time Warping (DTW) that measures similarity between time series by considering the temporal relationship between rotational vectors. Group (patients and healthy controls) and gesture category (meaningless, intransitive, and transitive), as well as, their interaction will be added as fixed effects, while a single intercept parameter estimated for each participant will be added as random effects. Covariates in the model will also be considered if demographic characteristics such as age, gender or education are different between patients and controls. In addition, differences in symptom severity and motor deficits between inpatient and outpatient participants will also be considered. The Kruskal–Wallis test will be used to assess such differences. In addition, we will apply partial correlation analyses using the spearman method to examine the relationship between gesture performance accuracy in VR with symptom severity, motor, socio-cognitive and community functioning scores, while controlling for medication. This will help in determining if gesture performance accuracy using VR in patients is linked to a specific domain or is generalized across multiple domains.

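### Separate medication-adjusted correlations cannot, by themselves, tell a domain-specific link from a generalized one; no between-domain comparison or joint model is described

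*Protocol article*

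**What the plan says.** Section 3 (Statistical analysis) plans "partial correlation analyses using the spearman method" to relate VR gesture accuracy to "symptom severity, motor, socio-cognitive and community functioning scores", "while controlling for medication". It then states the purpose: the results are to help show whether "gesture performance accuracy using VR in patients is linked to a specific domain or is generalized across multiple domains".

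Section 2.6 says "All clinical, motor, socio-cognitive and community functioning assessments can be found in Table 2". That table lists 3 psychopathology, 5 motor, 7 socio-cognitive and 4 community functioning instruments, 19 in all, plus self-reports. On sample size, section 2.1 says "We plan to recruit 60 schizophrenia patients and 60 age and gender matched controls over a 2-year period".

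The article describes no comparison of one domain's correlation with another's and no model holding several domains at once. It gives no significance threshold, no expected correlation and no criterion for calling a link specific or generalized.

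**The concern.** Calling a link specific to one domain is a statement about differences: this domain is related to accuracy, and the others are not, or are less so. Correlations computed one domain at a time estimate each relation but never the difference between two of them. A significant correlation in one domain and a non-significant one in another do not show that the two differ.

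A second gap works in the opposite direction. Symptoms, motor signs, cognition and functioning are likely to be correlated with each other. A domain with no relation of its own to accuracy will then correlate with it through a domain that has one. Adjusting for medication does not remove this.

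At stake is the substantive reading of the secondary analysis. The study could report a specific deficit when all domains are alike, or a generalized one when a single domain carries the relation.

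**Working it through.** **No figure to reproduce.** The article states no power, error rate or effect size for these correlations.

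**Inputs from the article.** 60 patients (section 2.1); Spearman partial correlation adjusted for medication, and four domains (section 3).

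**Assumptions.** Two-sided 0.05; medication as one covariate; one score per domain; a domain counts as linked if its correlation is significant; true rho and inter-domain correlation varied over the ranges shown.

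**Power of one correlation.** With one covariate, the Fisher z approximation has SE = sqrt(1.06/(60 - 4)) = 0.1376. At rho 0.3, atanh(0.3) = 0.3095 and 0.3095/0.1376 = 2.25, so power is about Φ(2.25 - 1.96) = 0.61. The same formula gives 0.31 at rho 0.2, 0.87 at 0.4 and 0.98 at 0.5. Simulation of the rank-based test gives about 0.30, 0.60, 0.85 and 0.97.

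**Hand check at rho 0.3 with four uncorrelated domains.** All four significant: 0.614^4 = 0.14. Exactly one: 4 × 0.614 × 0.386^3 = 0.14.

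**Scenario A: all four domains equally linked.** This is a fair test case, because the last paragraph of the Introduction hypothesizes links with all four. Simulated, inter-domain correlation 0.2 to 0.6:

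| True rho | Exactly one significant | All four significant |
|---|---|---|
| 0.2 | 22-35% | at most about 10% |
| 0.3 | 16-18% | 17-30% |
| 0.4 | 2-5% | more than half |
| 0.5 | under 1% | about 90% |

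At rho 0.3, two or more domains are significant in 70-79% of runs. Widening the inter-domain correlation to 0-0.7 gives exactly one in 18-42%, 14-18% and 1-5% at rho 0.2, 0.3 and 0.4, and all four in 12-36% at rho 0.3.

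**Scenario B: one domain directly linked, the other three related to accuracy only through it.** Each of those three has a true correlation with accuracy equal to the direct rho times the inter-domain correlation. For example, 0.5 × 0.7 = 0.35, without any contribution of its own. Share of runs with two or more domains significant:

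| Direct rho | Inter-domain 0.3 | 0.5 | 0.7 |
|---|---|---|---|
| 0.4 | 30% | 52% | 71-72% |
| 0.5 | 42% | 70% | 89% |

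Repeat simulations agree to within about one to two percentage points.

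**Reading the two together.** Stronger correlations reduce the error in A but increase it in B, so larger effects do not rescue the approach.

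**The case against.** The strongest defence is that this is a secondary analysis in a study labelled exploratory, and the wording is modest: the correlations only help in determining the pattern. That lowers the severity. It does not make separate correlations answer a comparative question, and since the article states both the method and the intended conclusion, this is not merely detail left to an unseen analysis plan.

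Four stronger readings are tempting, and the article does not support them.

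- *The correlations are unadjusted.* They are partial correlations controlling for medication. What is missing is adjustment of one domain for another.
- *The article fixes a faulty rule based on counting significant domains.* It fixes no rule. Judging links by significance is an assumption made here to give the problem a size; the investigators might use estimates and intervals.
- *The plan will usually report specificity when all domains are equally linked.* The article contrasts one domain with multiple domains. On that wording, two or three significant domains point to generalized, and at rho 0.3 two or more are significant in 70-79% of runs. Specificity becomes the usual result only if every outcome short of all four significant is called specific, and then only for rho of about 0.2 to 0.35 with domains not strongly correlated. On that loose count, the share falls to 29-49% at rho 0.4 and 8-10% at 0.5.
- *Lack of multiplicity control over 19 scales is a fault in its own right.* Nineteen independent tests would give 1 - 0.95^19 = 62% chance of at least one false positive. But the article is silent on error control, and a condensed article may leave that to the full protocol or analysis plan. It is not a separate ground here.

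**Conclusion.** The point holds in a limited form. Followed as written, the planned correlations do not distinguish a domain-specific from a generalized link, because domains are neither compared nor adjusted for each other.

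The error can go either way. A falsely specific reading (exactly one domain significant) is appreciable when true correlations are about 0.2 to 0.3 and rare from 0.4 upward. A falsely generalized reading is common when one domain carries the relation and the domains are correlated. These rates rest on the assumptions listed above, above all one score per domain and judgement by significance. They show the order of the problem and do not forecast this study's result.

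Grade: should be fixed. The primary group-by-gesture-category mixed model is not affected.

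**What to change.** 1. Form one standardized composite score per domain, so that domains with 3, 5, 7 and 4 instruments enter on equal terms.
2. Report the four medication-adjusted partial correlations with 95% confidence intervals.
3. Compare them directly, by bootstrap or a Steiger-type test for dependent correlations, or fit one joint model with all four domains and medication. The comparison asks whether one link is stronger; the joint model asks whether a domain contributes beyond the others, which is the issue in scenario B. State which question is meant.
4. Claim a specific link only if the interval for the difference from the other domains excludes zero. Allow inconclusive as a result, and do not take failure to find a difference as proof of a generalized link.
5. If none of this is wanted, delete the specific-versus-generalized sentence and present the correlations as descriptive.

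Cost: no new data, a few lines of code and a paragraph of text. The real drawback is precision. With 60 patients, an observed partial correlation of 0.3 has an approximate 95% interval of tanh(0.3095 ± 1.96 × 0.1376), or 0.04 to 0.52. For two uncorrelated domains, the difference on the Fisher z scale has a half-width of 1.96 × sqrt(2) × 0.1376 = 0.38, less if the domains are positively correlated. The comparison may therefore often be inconclusive, and the report should say so when it is.

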## 4. Trial status

Recruitment for the study begun November 1st 2022, and is expected to be completed November 2024. As of May 2023, we recruited 23 patients and 8 controls, and completed assessments for 19 patients and 7 controls.

## 5. Discussion

The crucial feature of this study is the implementation of a VR setup to assess real-time movements to objectively quantify gesture performance accuracy in schizophrenia patients and healthy controls. To date, assessment of gesture performance in schizophrenia patients is mostly based on categorical data, and doesn't take into account all the attributes and features associated with gesture performance. VR captures multidimensional data that may reveal hidden insights on the mechanisms attributed to gesture deficits in schizophrenia patients. If our VR setup proves to be successful in capturing and measuring gesture deficits in schizophrenia patients this has the potential to generate new knowledge regarding non-verbal communication that can help in designing therapeutic interventions to improve treatments for schizophrenia patients (36). Such treatments are valuable as there are often substantial costs to patients, their family and friends, caregivers and to the society as a whole (64). In the following section, we briefly discuss the types of therapeutic interventions available to schizophrenia patients, and discuss future directions on how VR can support and expand their impact.

Thus far, most treatments for schizophrenia heavily relied on pharmacological interventions, with heterogeneous results (23). Recent evidence suggests that neurostimulation (65–67), cognitive remediation therapy (52, 68–70) and social skills training (70, 71) promote neuroplasticity and can alleviate non-verbal communication deficits in schizophrenia patients, such as the evaluation and interpretation of emotional expressions, eye contact and body language but none are exclusive in tackling gesture deficits. In fact, therapeutic interventions specifically targeting gesture deficits and, in particular, gesture performance deficits in schizophrenia are limited. One recent study used a specific multimodal speech-gesture training that integrates non-verbal communication, working memory abilities and natural communication (72) to improve gesture processing in schizophrenia and showed significant improvements in patients' quality of life, which was significantly correlated with changes in the neural processing of abstract speech-gesture content (73). Another study, which combines neurostimulation and social cognitive remediation therapy to examine their effectiveness in improving gesture performance in schizophrenia is currently underway (68).

While conventional therapeutic interventions are essential in recovery, they are organized in accordance to one's environment, reaching only a portion of the patients who can benefit, and are strongly dependent on the availability and expertise of therapists. The application of VR in clinical settings can provide flexible, ecologically valid, reproducible and highly-controlled environments of real-life situations offering cost-effective exposure therapy in terms of time and expenses while reaching a much larger population. This coupled with the convenience and privacy it provides, clinicians have utilized VR in pain management, cognitive and motor rehabilitation in stroke and Parkinson's patients, and therapy and training exposure for patients suffering from anxiety, depression and psychosis (74–76).

VR use in schizophrenia has been successfully applied to alleviate auditory hallucinations and paranoid ideation (77, 78) to improve interpersonal communication by having patients interact with various characters with different behaviors, and help them acquire new social and interview training skills (79, 80). Patients in such treatments have previously expressed enjoyment and increased motivation when using VR (79, 81). However, no previous studies have explored the potential of VR in movement rehabilitation in schizophrenia patients in order to improve gesture performance. Evidence from neurological patients suggests that VR as a multifaceted system promotes motor learning, a process where the acquisition of newly learned movement skills via experience and practice induces a permanent change in one's ability to execute these newly learned movements (82). If our VR setup proves effective in measuring movement discrepancies during gesture performance in schizophrenia patients, it can be applied to generate new therapeutic interventions, specifically targeting gesture deficits using motor learning, and assess potential changes over time resulting from these interventions. Moreover, VR's adaptable and diverse technological features enable its integration with existing therapies like cognitive remediation therapy and social skills training. This integration can provide more accurate and objective measurements of naturalistic behaviors arising from ongoing interactions that cannot otherwise be quantified using traditional methods. This constitutes VR the ideal candidate in providing patients with an enjoyable and add-on alternative to help in retaining and transferring motor learning in their daily life (83, 84). These newly acquired movement skills can improve how schizophrenia patients express themselves to their family, friends', doctor, or therapist, and how they handle day-to-day tasks, thus enhancing their overall social communication and functioning, whilst promoting independence.

## 6. Limitations

The study does have certain limitations. First, this is a cross-sectional study measuring gesture performance accuracy in VR at a single time-point. Conducting longitudinal studies could offer a more comprehensive understanding of how gesture performance can progress over time in schizophrenia patients. Second, it is crucial to take into account the potential effects of antipsychotic medication on gesture performance. While we intend to account for antipsychotic medication use as a covariate in our analyses, it is important to acknowledge that patients might be on other types of medication that may still influence our findings. Third, although the optical body tracking was designed to avoid occlusion and reduce tracking discrepancies, tracking losses might still occur leading to potential inconsistencies in the data. Fourth, our application currently supports only gender-matched virtual bodies to substitute the participants' real body. However, in future updates, we aim to use personalized avatars that can consider ethnic characteristics as well. This enhancement could allow for accommodating potential variations in body ownership. This may be particularly important to address in patients with schizophrenia, whereas for healthy individuals it has been demonstrated that body ownership illusions can be induced over distinct virtual bodies, including different race (85–87).

## 7. Conclusion

The study aims to provide an objective measurement in assessing gesture performance accuracy in schizophrenia patients and healthy controls using VR. If this study proves to be successful it opens the possibility of utilizing VR paradigms to carry-out therapeutic interventions using motor learning elements to improve gesture deficits in schizophrenia patients and measure possible changes over time in response to these interventions. These types of interventions can be beneficial to other mental health disorders patients who exhibit gesture deficits such as depression (88, 89) or suffer from social cognitive deficits that interfere with non-verbal communication skills such as bipolar and autism spectrum disorders (90, 91).

## Ethics statement

The studies involving human participants were reviewed and approved by Kantonale Ethikkommision Bern (KEK 2021-02047). The patients/participants provided their written informed consent to participate in this study.
